## Abstract

**Background:**

Post-fistula-repair incontinence (PFRI) is a common complication of vesicovaginal fistula (VVF) surgeries. It entails continuous leakage of urine after successful VVF closure. Pelvic Floor Muscle Training (PFMT) plays a vital role in the management of PFRI, however, an evolving exercise approach is the Paula Exercise Method (PEM) which has shown a promising effect in stopping urinary incontinence, but there is no data on its effect on PFRI. This study therefore, proposes to primarily investigate the effect of PEM on urine leakage and secondarily, pelvic floor strength (PFS), quality of life (QoL), sexual function (SF), and mental health (MH) in women with PFRI.

**Methods:**

This is a study protocol for a randomized controlled trial. A total of 182 participants are expected to participate in the study after satisfying the inclusion criteria. The participants will be randomized into either PEM or PFMT study groups. The demographic data of all the participants will be recorded. Each participant will be assessed for urine leakage, PFS, QoL, SF, and MH at baseline and subsequently, at four, eight and 12 weeks of intervention.

Demographic parameters will be summarized using descriptive statistics. Continuous data will be computed for differences using inferential statistic of Analysis of variance, t-test and Man Whitney U as appropriate. All analyses will be performed using SPSS version 22.0 with probability set at 0.05 alpha level.

**Discussion:**

It is hoped that the outcome of this study will determine the effect of the Paula exercise method on urine leakage, pelvic floor strength, quality of life, sexual function, and mental health among women with post-fistula-repair incontinence and also provide evidence for the use of the Paula method in urinary incontinence.

*Trial registration*: Pan African Clinical Trials Registry (www.pactr.org), identifier PACTR201906515532827.

## Background

Vesicovaginal fistula (VVF) is an abnormal opening between the vagina and the bladder that occurs often during childbirth as a result of prolonged obstructed labour [1, 2]. This occurs following compression on the pelvis by the foetal head resulting in tissue necrosis. This creates an opening between the vagina and bladder which leads to constant urine leakage from the vagina [1–3]. It is the major type of obstetric fistula, accounting for about 90% of all obstetric fistula cases [1, 4]. It is also regarded as one of the major causes of morbidity among females in developing countries and some parts of developed countries [2, 5]. The consequences of VVF can be devastating, as it affects women physically, socially, economically and psychologically [3, 4].

A number of studies have noted the risks for developing VVF as including: illiteracy, poverty or low socio-economic status, childbearing at an early age, lack of access to antenatal care, lack of skilled or trained traditional birth attendants, and a malformed pelvis [3–8]. Obstetric VVF affects 2 million women worldwide, with a prevalence of 3 per 1000 women in sub-Saharan Africa [2, 5, 8]. In Nigeria, according to the Federal Ministry of Health [9], there are over 20,000 new cases of VVF yearly, in addition to the approximately 400,000–800,000 existing cases awaiting surgical repair. Over 85% of all cases of VVF are found in the north-western part of Nigeria [7, 10]; high incidences are reported in Kano, Katsina and Bauchi states in this region of the country [7].

Surgical interventions have been proven to be the effective management for VVF, especially in complex fistula, and in small fistula if conservative treatment fails [1, 11]. Unfortunately, some women pass through the devastating period of having the VVF and undergoing the surgical procedure, but do not regain continence [1, 12, 13]. The VVF repair may be satisfactory anatomically, but inadequate functionally, as some women present with urinary leakage (called post-fistula repair incontinence) even after a successful repair [12–16].

Post-fistula repair incontinence (PFRI) as reported in the literature, is one of the most common complications of VVF surgeries, where urine continues to leak (especially with exertion) after successful VVF closure [12, 13, 17]. This incontinent gap is poorly understood and is a source of frustration to fistula surgeons (and particularly the patients) [1, 16, 18–20].

Risk for developing PFRI depends on the site and type of fistula, as well as pelvic floor strength (PFS). Women with severe pelvic floor muscle (PFM) weakness are at risk of developing PFRI [21, 22]. According to Kayondo et al., type IIb fistulae are six times more likely to cause incontinence after successful repair than type I fistulae [22]. Also, women with circumferential fistula or larg fistulas are less likely to be continent after surgery [23]. PFRI also arises due to small bladder size/capacity following loss of the surface area of the bladder wall due to extensive fistula, neurologic damage, or due to the involvement of the urethral sphincter, especially if there is marked tissue loss and scarring [1, 8, 12]. Furthermore, PFRI occurs if there is loss of the sphincteric mechanism of the vesicourethral junction, and reduced bladder capacity or injury to the urethra [14, 20]. It has been reported that the risk of PFRI is 50% in women with minimal vaginal scarring and good bladder volume, while is 100% in women with reduced bladder volume and/or severe vaginal scarring [22–24]. Conservative interventions are the mainstay in the treatment of PFRI [11, 14, 20]; but unfortunately, supplementary surgery is prioritized over non-surgical options; the consequence of this is further deterioration of the condition [24]. It has however, been suggested that surgery should only be considered in persistent cases of PFRI or if the conservative treatment failed [12, 13].

Physiotherapy plays a vital role in the management of urinary incontinence (UI) and its associated symptoms through rehabilitation of the pelvic floor muscles (PFM), either directly or indirectly. Directly, the PFM can be rehabilitated through: pelvic floor muscle training (PFMT), biofeedback, cone therapy, and neuromuscular electrical stimulation [25, 26]; and indirectly through exercising other muscles of the body like the transverse abdominal muscles and circular or ring muscles (known as Paula Exercise Method), and also by patient education [27–29]. However, there is limited data on the role of physiotherapy on PFRI specifically. The available data mainly used pelvic floor muscles training (PFMT) [8, 13, 14, 17, 30]. And, to achieve positive effects of the PFMT, the exercise needs to be individualized and performed under professional supervision [21]. In addition, women find it difficult to voluntarily contract their PFM if it is weak even with proper instructions, and instead they end up contracting their abdominal, gluteal, and hip adductor muscles, and try to exaggerate inspiration which will often worsen their condition. Moreover, most of the VVF centres do not have physiotherapists or trained continent nurses to guide the women in performing the correct PFMT [23]. Even if there are professionals, teaching and monitoring the PFMT of patients individually may not be possible due to the high number of victims. Therefore, there is the need to find a conservative approach that can be performed with more ease and possibly in a group to accommodate the large number of the affected women and to encourage peer support, to help the affected women to get back to their normal life and minimize the need for another surgery.

The Paula exercise method also called circular/ring muscle exercise is a growing conservative method used in the treatment of urinary incontinence (UI) in general. It is an easy-to-perform approach, and has been tested to be effective in the management of UI and its associated complications in women without previous fistula repair [27, 29–31]. Practically, the Paula exercise method focuses on contracting and relaxing specific circular (or ring) muscles of the body in an effort to rehabilitate other damaged muscles of the body, because the body sphincters works together and their activity can affect one another due to oscillations in the spinal cord [27, 28, 31, 32].

The Paula method is considered an alternative to PFMT and has been found to exhibit comparable efficacy for urinary incontinence [31, 33], including demonstrable long-term effects [34]. A study demonstrated comparable effectiveness of PFMT and PEM on sexual function and quality of life in women suffering from stress urinary incontinence [31]. However, a systematic review reported limited evidence for alternative exercise regimens for the reduction of urinary leakage in women with stress urinary incontinence [35]. The review found methodological limitations in PEM as an alternative to PFMT. The limitations included the fact that one of the studies was a pilot study [35] with small sample size while the other subjected the control, i.e. the PFMT group, to below-optimal training, and the high loss to follow-up (up to 28%). Additionally, both studies were conducted by the same group of researchers. These factors obviously suggest the need for more studies with robust methodological approaches in diverse groups of researchers from distinct settings to investigate the efficacy of the Paula exercise method. This study aims to contribute to filling this gap and is therefore, targeted at investigating the effectiveness of the Paula exercise method in women with PFRI.

## Study objectives

The main objective of this study is to investigate the effect of the Paula exercise method on urine leakage among women who suffered post-fistula repair incontinence (PFRI). In addition, the study will investigate the following:Effect of the Paula exercise method on pelvic floor strength in women who suffered PFRI.Effect of the Paula exercise method on quality of life of women who suffered PFRI.Effect of the Paula exercise method on sexual function in women who suffered PFRI.Effect of the Paula exercise method on mental health in women who suffered PFRI.

## Methods

### Study design and sample

The research design for this study is a randomized controlled trial (RCT). It is a quantitative research in the form of pretest, posttest and follow-up design. The study will be a two-arm, outcome assessor-blinded RCT. The two-arms will comprise an intervention and a control. Following participants’ consent and baseline assessments, eligible participants shall be allocated randomly into either the intervention group (Paula exercise method) or the control group (pelvic floor muscle training). The proposed timeline for this study is 12 calendar months from participants’ enrolment to follow-up assessments; Table 1 below:

**Table 1 Tab1:** Study timeline from enrolment to completion

	Enrollment	Allocation	Post-allocation				Follow-up
Time point	− t	0	t0 (0 week)	t1 (4 weeks)	t2 (8 weeks)	t3 (12 weeks)	t4 (6 months)
Enrollment: eligibility screen informed consent allocation	X						
	X						
		X					
Intervention: Paula exercise (experimental group) Pelvic floor muscle training (control group)			X	X	X	X	
			X	X	X	X	
Assessments: baseline variables—age, weight, height, blood pressure, marital status, educational status, post fistula repair time	X	X					
Assessments: outcome variables [Primary outcome- urine leakage] [Secondary Outcome- pelvic floor strength, quality of life, sexual function, depression and anxiety]			X	X	X	X	X

### Setting

All participants will be recruited from Murtala Muhammad Specialist Hospital (MMSH) and Jahun General Hospital (JGH) in Kano and Jigawa states of Nigeria respectively. The training will be conducted at the physiotherapy departments of the two institutions. The MMSH is a major health institution in Kano State; it is a specialist and referral centre to all hospitals in Kano State and its neighbouring states. It has a bed capacity of eight hundred and twenty six (826), thirty (30) wards and units, nine (9) operating theatres, fourteen (14) clinics, and a staff strength of 1656. Similarly, JGH is a state hospital located in Jahun local government area of Jigawa State. It provides quality health services to people in Jigawa State and the neighbouring states. It is a 300-bed capacity hospital with diverse clientele who receive treatment from the different clinical departments of the facility.

### Participants

Participants in this study will comprise all women with PFRI attending the obstetrics and gynaecology departments of MMSH and JGH. However, only women who meet the study inclusion criteria will be screened and randomized into the experimental (Paula Exercise Method) and control (Pelvic Floor Muscles Training) groups. Participants will be screened for eligibility by the researcher and the research assistants. Participants will be considered eligible if: they have had the PFRI for more than 3 months, to ensure that healing has taken place [1, 14]; they present with a 1 g gain in weight following a pad test; they consent to participate through a written informed consent; they are not above the age of 50 because as women age changes occur in the bladder and pelvic structures that can increase the risk of developing incontinence [36]; they have no faecal leakage; they have not had previous rectal surgery; they are not receiving any other alternative PFM rehabilitation at the point of recruitment; and urinary infection is ruled out because it affects the integrity of the pelvic organs [37].

After screening for eligibility, a cough test will be used to differentiate the type of incontinence. In the cough test, if urine leakage coincides with the cough, it is classified as stress incontinence (SI), however, if the leakage is delayed till after the cough, it is urge incontinence. No leakage after the cough signifies that it is overflow and functional incontinence [38].

### Sample size

The sample size of this study was estimated based on the findings of a pilot study. We conducted a pilot study to test the adequacy and feasibility of this protocol as well as to determine the sample size required for this study. The pilot study participants were recruited after being certified as eligible to participate using the specified study inclusion criteria. Recruitment was conducted by reviewing records of the outpatient urology clinic on a weekly basis. A total of 30 women with post fistula repair incontinence participated in this pilot study. The 30 subjects were randomly assigned into the two arms of the study resulting into 15 participants in each arm of the pilot study (Paula Exercise Method and Pelvic Floor Muscle Training groups). All participants were assessed at baseline before randomization and prior to the commencement of intervention, post intervention (outcome). The primary outcome of interest is Urine leakage. The programme was structured for 4-weeks of daily routine activities in both groups. The detail of urine leakage assessment is described later in the manuscript as the primary outcome measure.

In this pilot study the mean age of participants was 29.9 ± 9.4, the median Urine leakage score for PEM and PFMT was 4.53 g and 21.61 g respectively. We computed Mann Whitney U for the data because the data was not normally distributed. Result for an independent two groups non-parametric test indicated significance (*U* = 38.00,* p* = 0.020) with an effect size of *Ƞ*^2^ = 0.32.

Using the outcome of the pilot study and according to a power calculation to detect a between-group difference, of 0.3 effect size for two independent means Mann Whitney U in urine leakage (UL) with 90% power at α = 0.05, a total sample size of 166 was generated. This suggests a total of 83 participants in each group. A 10% attrition rate will be considered, therefore, 182 participants will be recruited giving 91 participants in each group. The recruitment of participants from the two hospitals would be accomplished by: involving the surgeons from the departments of obstetrics and gynaecology of both hospitals who are involved in performing the fistula repairs (in the recruitment); and reviewing hospital registry and subsequently contacting patients whose records are available through individual phone contacts.

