## Data analysis

Microsoft Excel will be used to record all the data obtained before being exported to the Statistical Package for Social Sciences (SPSS). Descriptive and inferential statistics will be used to analyse the data. All study parameters will be summarized using descriptive statistics of frequency, mean, standard deviation, and percentage. Factorial ANOVA will be used to determine between-group differences/interactions in the study groups from the pre to the follow-up study period for PFS and UL among study participants. The Wilcoxon signed-rank test will be computed to determine differences between the pre, post and follow-up intervention for SF, ML and QoL scores in both the experimental and control groups. The independent t-test will be used to determine the difference in the post intervention PFS and UL scores between the experimental and control groups, while Mann–Whitney U will be used to determine the difference in the post intervention for SF, ML and QoL scores between the experimental and control groups. The magnitude of the differences between the groups will be determined by calculating the effect sizes. Missing data will be handled through multiple imputation. All analyses will be performed with probability set at 0.05 alpha level.

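### The stated 90% power does not follow from an effect size of 0.3 read as a standardised mean difference, and the metric and sidedness are not given

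*Protocol article*

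**What the plan says.** All the inputs stand in the Sample size section of the protocol article.

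- **Pilot.** There were 15 women per arm. Urine leakage was not normally distributed and was compared by Mann-Whitney: U = 38.00, p = 0.020, "effect size of *Ƞ*^2^ = 0.32".
- **Link to the pilot.** The calculation is introduced as "Using the outcome of the pilot study and according to a power calculation to detect a between-group difference".
- **Planned effect and result.** The effect is "0.3 effect size for two independent means Mann Whitney U in urine leakage (UL) with 90% power". The result is given as "with 90% power at α = 0.05, a total sample size of 166 was generated", and then "This suggests a total of 83 participants in each group".
- **Attrition.** "A 10% attrition rate will be considered, therefore, 182 participants will be recruited giving 91 participants in each group".

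The section does not say what kind of effect size 0.3 is, or whether the test is one-sided or two-sided. The Data analysis section adds only "All analyses will be performed with probability set at 0.05 alpha level". For urine leakage it plans an independent t-test and a factorial ANOVA, and it reserves Mann-Whitney for sexual function, mental health and quality of life.

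**The concern.** An effect size for two independent means is ordinarily a standardised mean difference. A value of 0.3 on that scale is small, and 166 women are far too few for 90% power. The sentence ties the figure to the pilot, but the pilot's effect size is a share of variance on a different scale. A reader therefore cannot tell whether the trial was sized for a small, moderate or very large difference.

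This paragraph is the article's only justification for enrolment, and the comparator is active. If d = 0.3 was meant, a null result could be taken as 90%-power evidence that the two exercise programmes do not differ, when the chance of detecting that difference was about one in two.

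**Working it through.** **Inputs** (Sample size section): effect size 0.3, power 90%, alpha 0.05, 1:1 allocation, 83 per arm, 10% attrition; pilot U = 38.00 with 15 per arm, eta-squared 0.32. Two-sided testing is assumed unless stated. z(0.975) = 1.960, z(0.90) = 1.282, and the squared sum is 10.507.

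**1. Trying to reproduce 166 with 0.3 as Cohen's d**
- Normal approximation: n per arm = 2 × 10.507 / 0.3² = 233.5, so 234 per arm and 468 in total.
- t-test (noncentral t): 234.5, so 235 per arm and 470 in total.
- Mann-Whitney, normal data (efficiency 3/π = 0.955): 234.5 / 0.955 = 245.5, so 246 per arm and 492 in total.
- One-sided: 382 (t-test) or 402 (Mann-Whitney).

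**2. Power at 83 per arm for d = 0.3**
- Noncentrality: 0.3 × √(83/2) = 1.93, which falls just short of the critical value of about 1.96, so power is a little under one half.
- Two-sided: 48.5% (t-test), 46.7% (Mann-Whitney; 46.9% by simulation).
- One-sided: 61.0% and 59.3%.

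**3. Other metrics, 0.3 taken exactly, 90% power, two-sided**

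| Reading of 0.3 | Conversion | Total N |
|---|---|---|
| Cohen's f, two groups | d = 2f = 0.60 | 120 (t), 126 (Mann-Whitney) |
| Correlation r | d = 2r/√(1 − r²) = 0.629 | 110, 114 |
| Rank-biserial | P = (1 + 0.3)/2 = 0.65; Noether: 10.507/(3 × 0.15²) = 155.7 | 156 |
| Eta-squared | d = 2√(0.3/0.7) = 1.31 | 28 |

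None of these gives 166. A rank-biserial of 0.29 (P = 0.645) gives 10.507/(3 × 0.145²) = 166.6, in effect the stated figure.

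**4. What 83 per arm detects with 90% two-sided power**
- d = 0.506 (t-test) or 0.518 (Mann-Whitney). By Noether's formula this is a probability of less leakage of about 0.645.

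**5. Pilot figures**
- Eta-squared 0.32 as d: 2√(0.32/0.68) = 1.37, which would need about 26 women.
- U = 38 with 15 v 15: mean 15 × 15/2 = 112.5; SD = √(225 × 31/12) = 24.11; z = (112.5 − 38)/24.11 = 3.09; two-sided p = 0.002.
- z²/30 = 9.55/30 = 0.318. U therefore agrees with the reported eta-squared, and the p-value is the figure that does not fit.

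**6. Attrition**
- 182 × 0.9 = 163.8, below 166.
- 166/0.9 = 184.4, or 186 for equal arms. The printed 182 is 166 × 1.1 = 182.6 rounded down.

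**The case against.** The strongest reply is that the shortfall depends on a reading the article never states. The section ties 0.3 to a Mann-Whitney test, for which a rank-biserial is a natural metric, and gives it to one decimal. A rank-biserial of 0.29 rounds to 0.3 and yields 166. A factorial ANOVA with f = 0.3 and 3 numerator degrees of freedom also comes close, at 162 (164 if balanced). On the alternative metrics 83 per arm is adequate: at least 90% power for a rank-biserial of 0.3, about 96% for f, 98% for r, and over 99.9% for eta-squared 0.3. The pilot data were also not normal, so calculations on normal data are approximate.

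Much of this stands. A reader might infer that no sensible reading gives 166, or that the trial is simply underpowered; the article supports neither. A reader might also infer that the pilot's eta-squared was entered as d. That cannot explain the figure, since d of about 0.3 returns 470 to 492.

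The reply does not clear the paragraph. The phrase about two independent means favours d, and the pilot's own rank-biserial is 1 − 2 × 38/225 = 0.66, so 0.29 does not come from there. The ANOVA route is not the test the section names. Non-normality does not close the gap under d = 0.3: a Laplace distribution, the most favourable tried, still needs 314 women two-sided, with 65% power at 83 per arm.

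The attrition gap is fairly called minor: about two women, with negligible effect on power. The pilot p-value does not enter the calculation.

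**Conclusion.** The concern holds conditionally. If 0.3 is Cohen's d, two-sided, with near-normal data, the stated size gives 47-48% power rather than 90%, and 90% would need 470 to 492 women. One-sided testing raises power only to 59-61%. If another metric was meant, the size may be adequate, but the article does not say so and the planned effect cannot be identified from it. The pilot's eta-squared of 0.32 does not justify a d of 0.3.

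Two errors depend on none of this: 10% loss from 182 leaves about 164 women, short of 166, and the pilot p-value disagrees with its own U by a factor of ten. The test in the sample size statement also differs from the tests planned for urine leakage.

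**What to change.** Rewrite the Sample size paragraph, leaving enrolment unchanged.

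1. Name the effect-size metric, the sidedness and the test. Make the test agree with the urine leakage analysis in the Data analysis section (t-test and factorial ANOVA), or change that section to match.
2. State what the size delivers: 83 per arm gives 90% two-sided power for d of about 0.51 (t-test) or 0.52 (Mann-Whitney; probability of less leakage about 0.645). If d = 0.3 was meant, state that power is about 47-48%.
3. State that the planned effect is not the pilot's eta-squared, or convert that value properly and say why a smaller effect was chosen.
4. State that about 164 women remain after 10% loss from 182.
5. Correct the pilot p-value to about 0.002, or correct U if that is the misprint; in that case recheck eta-squared, which agrees with the present U.

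The cost is one reworded paragraph and possibly a matching edit to the Data analysis section. No further women are needed. The downside is that the stated detectable effect may become less favourable.
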